#### **7.2.2 Sample Size**

The total sample size needed is 130 subjects. 65 intervention and 65 matched control group

#### **7.2.3 Interim Analyses**

An Interim Analyses is not applicable to this study.

#### **7.2.4 Missing Data**

For each primary efficacy endpoint, missing values will be replaced by the average of all non-missing values at that visit (rounded to an integer value) for the treatment groups being compared. A second confirmatory analysis will treat a missing value as a non-response. There will be no other imputation for missing data in the efficacy analyses.

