## **7.2 Statistical Methods**

### **7.2.1 General Statistical Methods**

For all primary and secondary outcomes, data will be analyzed using analysis of covariance (ANCOVA). Dependent variable will be change from baseline at three-month post-test, with treatment group as the independent variable, and baseline dependent variable as the covariate. Missing data will be imputed using last observation carried forward (LOCF). Effect sizes will be calculated using Cohen's d: mean differences divided by pooled standard deviation. For the primary outcome, change in total burnout, the significance level will be set at  $p < .05$ , two-tailed. For all secondary outcomes,  $p < .01$ , two-tailed, will be used (to compensate for multiple comparisons).

The primary population for analyses of efficacy data will be ITT population. A supportive analysis will be presented for the PP population if this is significantly different from the ITT population. Continuous data will be summarized by using descriptive statistics (number, mean, median, standard deviation, minimum, and maximum).

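### Sections 7.2.1 and 7.2.4 fix two incompatible single-imputation rules for the same primary endpoint, and add a non-response analysis that no endpoint supports

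*Protocol*

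**What the plan says.** Section 7.2.1 sets the scope: "For all primary and secondary outcomes, data will be analyzed using analysis of covariance (ANCOVA"). The endpoint is a continuous change score: "Dependent variable will be change from baseline at three-month post-test, with treatment group as the independent variable". The same paragraph then states "Missing data will be imputed using last observation carried forward (LOCF"). Total burnout is tested at the 5% two-sided level, and the primary population is intention-to-treat, so people without a 3-month value have to be handled somehow.

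Section 7.2.4 gives a different rule for each primary efficacy endpoint: "missing values will be replaced by the average of all non-missing values at that visit (rounded to an integer value"), with the average taken "for the treatment groups being compared". It continues "A second confirmatory analysis will treat a missing value as a non-response" and closes with "There will be no other imputation for missing data in the efficacy analyses".

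Sections 3.2 and 6.2 schedule the outcomes at baseline, 2 weeks, 1 month and 3 months. Section 7.2.2 gives 65 people per group and states no dropout rate, SD or effect size.

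**The concern.** There are three faults, and all lie in what the protocol fixes, not in detail left to a SAP.

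- **Contradiction.** Change in total burnout falls under both sections. The closing sentence of Section 7.2.4 excludes the LOCF that Section 7.2.1 requires. LOCF cannot be rescued as a sensitivity analysis either, because Section 7.2.4 names its only second analysis and that is a different one.
- **Ambiguity inside Section 7.2.4.** The phrase about the groups being compared can mean one mean over both groups or one mean for each group. The first pulls the arms together. The second leaves the difference alone but counts invented values as data.
- **An analysis with no definition.** Non-response has no meaning for a change score analysed by ANCOVA, since no section sets a responder threshold.

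The primary estimate, interval and p-value would therefore depend on which section the analyst follows, and that choice could be made after seeing the data. Unequal dropout is plausible, though the protocol gives no figure: Section 5 asks the meditation group to attend sessions and practise twice a day, and asks nothing comparable of controls. The 2-week and 1-month data, which could inform the missing values properly, enter the primary analysis only through LOCF.

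**Working it through.** **Inputs.** From the protocol: 65 per group, ANCOVA of 3-month change on group with baseline as covariate, 5% two-sided. Assumed, because the protocol gives none of them: score SD 10, correlation between visits 0.5 to 0.7, true effect 0 or −5 points (0.5 SD), half of the effect present at 1 month, and 10% to 30% of 3-month values missing at random. Each setting had 3,000 simulated trials.

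**What each rule should do.** Let δ be the true difference, *m* the fraction missing in each arm, and *f* the share of the effect already present at the visit carried forward.

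- Pooled visit mean: each arm keeps (1 − *m*) of its own mean and takes *m* of a common value, so the estimate is (1 − *m*)δ. At *m* = 0.20 this is 0.80 × (−5) = −4.0.
- By-group visit mean: the estimate stays at δ, but the residual variance is too small and the sample size too large, so the standard error is understated.
- LOCF: the estimate is δ[(1 − *m*) + *mf*]. At *m* = 0.20 it is −4.0 from baseline (*f* = 0) and −5 × (0.8 + 0.1) = −4.5 from 1 month (*f* = 0.5).

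**Simulated results, correlation 0.5.** Estimates are for a true difference of −5.

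| Missing per arm | Observed values only | Pooled mean | LOCF from baseline | LOCF from 1 month | By-group mean: model SE / true SE | By-group mean: type I error |
|---|---|---|---|---|---|---|
| 10% | −5.00 | −4.50 | −4.49 | −4.74 | 1.47 / 1.66 | about 0.08 |
| 20% | −4.99 | −3.99 | −4.00 | −4.51 | 1.41 / 1.80 | 0.122 |
| 30% | −4.96 | −3.46 | −3.46 | −4.26 | 1.34 / 1.91 | 0.161 |

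The estimates match the formulas. The type I errors follow from the standard errors: at 30% missing, 1.96 × 1.34 / 1.91 = 1.375, and the two-sided normal tail beyond 1.375 is 0.169, against 0.161 simulated. With correlation 0.7 the by-group type I errors are 0.077, 0.122 and 0.180. ANCOVA on observed values keeps type I error between 0.045 and 0.058 throughout.

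**Confidence interval coverage.** With correlation 0.6 and a true effect of 0.50 SD, the pooled mean gives 0.40 SD with 88% coverage at 20% missing, and 0.35 SD with 78–79% coverage at 30%. The nominal figure is 95%.

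**LOCF with drift and unequal dropout.** If both arms change by τ over 3 months and there is no true effect, the false difference has size (difference in missing fractions) × (share of the change not yet seen) × τ. With 30% against 10% missing, τ = 4 points and baseline carried forward, this is 0.20 × 1 × 4 = 0.80 points; the simulation gave 0.77 and type I error 0.087. Carried from 1 month with half the change seen, it is 0.20 × 0.5 × 4 = 0.40; the simulation gave 0.38 and type I error 0.052. With values carried from 2 weeks or 1 month and a linear trend of 0.5 to 0.8 SD, the bias is 0.07 to 0.12 SD and the type I error about 7.5% to 13%.

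**The non-response analysis.** Setting the two sections side by side is enough. Section 7.2.1 defines a continuous dependent variable, Section 7.2.4 calls for a category, and no section converts one to the other.

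**The case against.** The conflict in the text is hard to dispute, so the best defence is that its practical effect is small.

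- The pooled mean, arguably the more natural reading of Section 7.2.4, keeps type I error near 5% and costs little power: 0.84 against 0.88 for observed values at 20% missing, and 0.77 against 0.83 at 30% (correlation 0.6).
- LOCF inflates type I error only when scores drift and dropout differs. With 30% against 10% missing and no trend it is 5.2%; with a 0.2 SD trend, 5.4%; with 15% against 5% missing and a 0.5 SD trend, 5.8%.
- The protocol gives no attrition figure, the study lasts 3 months, and Section 6.2 allows virtual assessment. At 5% missing, coverage under the pooled mean and LOCF is 94–95%, and type I error under the by-group mean is 6.1%.
- Non-response could be read as zero change.
- The simulations support unimputed analysis when data are missing at random within arms. They did not test a repeated-measures model, and they ignore that the groups are matched and not randomised.

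These points stand as limits on size, and the figures must be read as conditional. They do not remove the contradiction, the unclear averaging or the missing responder definition, none of which depends on a dropout rate. A test with the right size is also little comfort when the estimate and its interval are wrong. The zero-change reading is not in the protocol.

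**Conclusion.** The point holds and must be fixed before any outcome data are examined. The protocol fixes two rules that exclude each other for its primary endpoint, one of them with two readings, and an analysis that cannot be run as written.

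Following any of the rules gives a worse answer than leaving the missing values unfilled. With 10% to 30% missing at random and 65 per arm, the effect shrinks by 10% to 30% (pooled mean, or LOCF from baseline) or by about 5% to 15% (LOCF from 1 month with half the effect present). Under the by-group mean, type I error rises to between 8% and 18%. LOCF bias under no effect needs both a secular trend and unequal dropout. All sizes rest on assumed missingness, correlation and trajectory, and are minor at about 5% missing.

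**What to change.** Delete the LOCF sentence in Section 7.2.1 and the whole imputation rule in Section 7.2.4, including the non-response analysis (or define response if that analysis is wanted). Amend the ANCOVA sentence in Section 7.2.1 to match.

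Name one primary method: a mixed model for repeated measures on change at 2 weeks, 1 month and 3 months, with group, visit, group-by-visit, baseline and baseline-by-visit terms and an unstructured covariance. The primary estimate is the group contrast at 3 months, so the planned baseline-adjusted comparison is kept. The model assumes data are missing at random, so add one sensitivity analysis: multiple imputation with a delta (tipping-point) shift in the meditation arm. Neither step addresses confounding from the non-randomised design, which is a separate matter.

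The cost is protocol and SAP wording and a little more programming, with no new data. With much dropout the confidence interval will be wider than under single imputation, and that width is honest.

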#### **7.2.5 Subject Disposition**

Subject disposition will be recorded. The numbers and percentages of enrolled subjects who completed the study and discontinued from the study will be provided, as well as reasons for earlier discontinuation.

#### **7.2.6 Demographics and Baseline Characteristics**

Demographic data and medical history will be summarized by means of descriptive statistics and frequency tables, stratified by treatment and age group.

#### **7.2.7 Procedure Compliance**

Compliance will be measured by adherence to treatment regimen in the subject diary.

#### **7.2.8 Concomitant Medications and Treatments**

The frequency and percentage of subjects with concomitant medications and treatments will be summarized by coded drug class and preferred term for each treatment group.

### **7.3 Source Documents**

The full dataset will be collected for all subjects enrolled. All required data for this study will be collected on paper source document worksheets. The collected data will be entered into a validated database. Database lock will occur once quality assurance procedures have been completed.

Source data is all information, original records of clinical findings, observations, or other activities in a clinical trial necessary for the reconstruction and evaluation of the trial. Source data are contained in source documents. Examples of source documents include hospital records, office charts, memoranda, evaluation checklists, photographs, and subject files.

All procedures for the handling and analysis of data will be conducted using good computing practices meeting USFDA guidelines for the handling and analysis of data for clinical trials.

### **7.4 Data Capture**

Data will be captured on CRFs. CRFs are the primary data collection instrument for the study. All data on the CRF will be recorded, and all missing data must be explained. All data collected for the study and entered into the CRF must be traceable to a source document.

The Investigator will review, approve, and sign off on the CRFs. The Investigator's signature will serve as a testament of the Investigator's responsibility for ensuring that all clinical data entered on the CRF are complete, accurate, and authentic. The CRF data is entered into a validated database.

## **8 ETHICAL, LEGAL AND QUALITY ADMINISTRATIVE ASPECTS**

### **8.1 Good Clinical Practice**

The procedures set out in this study protocol are designed to ensure that the individual treatments as well as the investigator abide by the principles of the Good Clinical Practice (GCP) guidelines of the ICH. The study will be carried out to abide with local legal and regulatory requirements.

Both Sponsor and Principal Investigator confirm this by signing this study protocol (see Page 2-3).

### **8.2 Changes in Statistical Methods**

All changes in statistical methods that are described in the statistical analysis plan (SAP) will be documented in the clinical study report.

### **8.3 Informed Consent**

Before being admitted to the study, informed consent will be obtained from each subject (or his/her legally authorized representative) according to the regulatory and legal requirements of the United States. This consent form must be dated and retained by the investigator as part of the study records.

Should a protocol addendum be made, the subject consent form may be revised to reflect the changes of the protocol.

If the consent form is revised, it is the responsibility of the investigator to ensure that an amended consent is reviewed and approved by the IRB. The approved amended consent form should be signed by all subjects subsequently entered in the study and those currently in the study.

The investigator will not undertake any investigation specifically required only for the clinical study until valid consent has been obtained. The terms of the consent and when it was obtained must also be documented in the CRF.

#### **8.4 Approval of Study Protocol**

Upon finalization of the original study Protocol, the Investigator Signature Page and Sponsor Signature Page are to be executed by each party representative as an acceptance and agreement of the Protocol.

Before the start of the study, the study protocol and/or other appropriate documents will be submitted to the IRB in accordance with local legal requirements.

The sponsor and the investigator must inform each other in writing that all ethical and legal requirements have been met before the first subject is enrolled in the study.

#### **8.5 Confidentiality**

All study findings and documents will be regarded as confidential.

The anonymity of participating subjects must be maintained. Subjects will be identified on CRFs and other documents by their initials, birth date, and subject number.

#### **8.6 Ethics Committee and Regulatory Authorities**

Before enrollment of subjects into this study, the protocol, ICF and any promotional material or advertisements will be reviewed and approved by the appropriate IRB and regulatory authorities, where applicable. The study will commence only when the committee has approved the protocol or a modification thereof and a copy of the approval letter is received.

It is the investigator's responsibility to obtain IRB approval for the protocol and all subsequent major changes, in compliance with local law.

#### **8.7 Monitoring**

The study monitor and/or other authorized representatives of the Sponsor is/are responsible for monitoring that each study site conducts the study according to the protocol, SOPs, other written instructions, Code of Federal Regulation (Title 21, CFR Part 812) and applicable regulatory guidelines. The investigator will permit the study monitor or other authorized representatives to visit the study site at appropriate intervals to observe the progress of the study, review study records/documentation, and ensure that informed consent has been obtained for each subject prior to performing any study procedure.

## **8.8 Auditing**

The Sponsor and/or Sponsor's representatives may conduct audits (quality assurance) to evaluate study conduct and compliance with the protocol, SOPs, other written instructions/agreements, Code of Federal Regulation (Title 21, CFR Part 812) and applicable regulatory guidelines/requirements. The investigator will permit auditors to visit the study site. The quality assurance auditor will have access to all medical records, the investigator's trial-related files and correspondence, and information in the informed consent documentation of this clinical trial.

